### Statistical analysis

2.11

All statistics were performed by independent statisticians using SPSS software (version 24.0, SPSS Inc., Chicago, IL, USA). The primary and secondary outcomes will be analyzed based on the intention-to-treat principle. Primary outcome analysis will be adjusted for baseline VAS and other prespecified covariates using ANCOVA or multiple linear regression if baseline imbalance is observed. Based on MCID of 1.5 points, the proportion of participants achieving MCID will be calculated. Occupation (sedentary vs. non-sedentary work) will be included as a stratification variable in WPAI-SHP analysis. All between-group comparisons will base on the change score of a specific time point and the baseline. Baseline characteristics will be summarized in a table and compared between groups to assess comparability. Missing values for dropout cases will be imputed using either the last observation carried forward method if the dropout rate is below 5% or the multiple imputation method for a dropout rate of 5% or higher. Descriptive statistics will be presented as mean ± SD for continuous variables that follow a normal distribution and as median (IQR) for those that do not follow a normal distribution, based on the results of normality tests. For ordinal variables, the data will be presented as median (IQR) or frequency (*n*, %) depending on the nature of the data. Categorical variables will be summarised as *n* (%). To analyse trends over time and the interaction between groups and times, two-way repeated measures analysis of variance will be used to compare clinical data at multiple observation time points.

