### Study design

2.1

This study is a randomized, assessor-blinded, single-center, two-arm, parallel-group superiority trial. The protocol was approved by the Ethics Committee of Yueyang Hospital of Integrated Traditional Chinese and Western Medicine, Shanghai University of Traditional Chinese Medicine (project number: 2023-143), and registered at the Chinese Clinical Trial Registry (ChiCTR2300073680). This study will follow the strict criteria outlined in the Consolidated Standards of Reporting Trials (CONSORT) and the Standard Protocol Items: Recommendations for Interventional Trials (SPIRIT) guidelines.

A total of 110 participants will be recruited from the Tuina Department of Shanghai Yueyang Hospital and randomly assigned (1:1) to either the Baduanjin group or the TCB group. The trial includes an 8-week intervention period and a 24-week follow-up. Baseline characteristics will be collected prior to randomization, and outcomes (pain, functional impairment, quality of life, adverse events) will be assessed at weeks 8, 20, and 32. The study procedures are illustrated in a flowchart (Figure 1), with the intervention and outcome schedule detailed in Table 1.

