### Participants recruitment

2.2

Participants will be recruited through posters in the Tuina Department and advertisements on WeChat, the largest social media platform in China. The poster includes the project title, participant inclusion and exclusion criteria, and contact information, including the recruiter's phone number, WeChat QR code, and address.

The clinical research coordinator (CRC) is responsible for explaining the study protocol and eligibility criteria and conducting a preliminary eligibility assessment for interested individuals. Potentially eligible participants will receive informed consent documents via email, WeChat, or in person, with sufficient time provided for review before making a decision. Eligible participants who confirm interest will attend a baseline visit, where an investigator will review the study protocol, reconfirm eligibility, and obtain written informed consent. To mitigate potential recruitment barriers related to access to Tuina therapy, participants randomized to the Baduanjin group will be assured free Tuina therapy upon completion of the trial. Baseline assessments will include all primary and secondary outcomes along with demographic data, after which participants will be randomized.

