### Withdrawal, dropout and removal criteria

2.5

Participants may withdraw from the trial at any time or be discontinued under the following circumstances, as determined by the clinical Data Monitoring Committee (DMC):
Clinically significant exacerbation of NCNP symptoms that severely impairs daily functioning or safety.Unanticipated serious adverse events or complications occur during the trial period, including trauma, allergic reactions, or worsening pain.Occurrence of other serious illness precluding continued participation, such as stroke, hospitalization, surgical interventions, or emergency care.Unblinding for emergencies.Withdrawal deemed necessary at the discretion of the researchers.Participants request to withdraw from the study due to a loss of interest, scheduling conflicts or other personal reasons.We will strive to contact participants who withdraw for any reason to acquire follow-up data and ensure their safety post-trial.

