### Sample size calculation

2.7

The sample size was determined for the primary outcome, mean pain intensity over the past week measured by the 0–10 VAS at 8 weeks post-randomization. We made an assumption of the anticipated between-group mean difference and standard deviation (SD) for the primary outcome (VAS) based on both literature and internal review of electronic patient records. An effect size of −1.2 points (95% CI, −1.6 to −0.8) was reported for tuina therapy combined with Yijinjing exercise (24) (a different exercise than Baduanjin, but also based on traditional Chinese exercise) compared with tuina therapy alone. Previous literature confirmed that for the measurement of bone and joint pain, 1.5 points can represent clinically important difference (MCID) (25). Due to the lack of direct previous research results on Tuina with or without Baduanjin, we set the smallest threshold difference than the results from literature or real-world data suggest. Therefore, a between-group difference of −1.5 in mean change at Week 8 and standard deviation1.1 to calculate the sample size. Calculations were performed using PASS 15 software with reference to Sample Size Calculations in Clinical Research (26). Assuming two groups, a two-sided significance level of 0.05, 80% power, and a 80% follow-up rate, 55 participants per group were required, yielding a total sample size of 110.

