#### Primary outcome

2.9.1

The primary outcome is the self-reported average pain intensity over the past week at week 8 post-randomization, assessed using the VAS. VAS is a 10-cm horizontal scale anchored by [0] on the left end, indicating “no pain”, and [10] on the right end, indicating the “worst pain”. Higher scores reflect greater pain intensity relative to baseline (27). The VAS was demonstrated to be a valid, responsible, concise and easily interpreted outcome measure with intraclass correlation = 0.92 (28).

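### The 5% dropout switch to last observation carried forward would score a participant with no week-8 VAS as exactly unchanged; the effect is bounded, and the branch should be deleted

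*Protocol article*

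**What the plan says.** Statistical analysis (2.11) fixes two methods and a threshold: missing values are "imputed using either the last observation carried forward method if the dropout rate is below 5% or the multiple imputation method", the second branch being "the multiple imputation method for a dropout rate of 5% or higher". The same section bases between-group comparisons on change from baseline, follows intention to treat, and reports the proportion reaching a 1.5-point improvement.

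On timing, Primary outcome (2.9.1) states: "The primary outcome is the self-reported average pain intensity over the past week at week 8 post-randomization". Study design (2.1) says that "outcomes (pain, functional impairment, quality of life, adverse events) will be assessed at weeks 8, 20, and 32". Participants recruitment (2.2) places the preceding measurement before allocation: "Baseline assessments will include all primary and secondary outcomes along with demographic data, after which participants will be randomized". Table 1 shows VAS at screening and at weeks 8, 20 and 32 only, and Intervention (2.8) adds nothing but attendance logs during treatment.

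Two further places bear on the point. Sample size calculation (2.7) assumes "a 80% follow-up rate". Withdrawal, dropout and removal criteria (2.5) lists among the reasons for discontinuation "Clinically significant exacerbation of NCNP symptoms that severely impairs daily functioning or safety", and ends with a commitment to try to obtain follow-up data from anyone who withdraws.

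**The concern.** LOCF needs a post-baseline value to carry. At week 8 there is none, so at the primary time point it amounts to baseline carried forward. The imputed change is zero whatever happened to the participant. Someone who left after improving loses the improvement. Someone withdrawn for exacerbation, whose week-8 score could not be obtained, is scored as unchanged when the true change may be a worsening. Either way the value enters the analysis as if it had been measured, and the participant counts as a non-responder.

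The direction of the bias depends on who leaves and from which arm. Participants know their allocation (2.6), and section 2.2 treats access to Tuina as a possible recruitment barrier, so uneven loss is not far-fetched. Among participants who would have improved, losses concentrated in the Baduanjin arm make the combined treatment look better, and losses in the combined arm make it look worse. LOCF therefore cannot be defended here as reliably conservative.

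**Working it through.** **Inputs from the protocol:** 55 per arm, 110 in total; planned difference −1.5; SD 1.1; two-sided 5% level; 80% follow-up (all 2.7); responder threshold 1.5 points and imputation threshold 5% (2.11). **Assumptions, not in the protocol:** the dropout rate is counted over all 110; participants who are lost would on average have improved as much as their arm; mean improvement is as stated in each step.

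**1. The plan's own loss figure.** 0.20 × 110 = 22 lost, leaving 44 per arm. That is well inside the multiple-imputation branch.

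**2. Where the switch falls.** 5/110 = 4.55% gives LOCF; 6/110 = 5.45% gives multiple imputation. LOCF can therefore affect at most 5 participants.

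**3. How likely the LOCF branch is.** Binomial probability of at most 5 losses among 110:

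| True dropout rate | Probability |
|---|---|
| 4% | 0.72 |
| 5% | 0.53 |
| 6% | 0.35 |
| 8% | 0.12 |
| 10% | 0.03 |
| 20% (planned) | 0.000003 |

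**4. The imputed value.** The last VAS before week 8 is the baseline, so change = baseline − baseline = 0.

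**5. Shift in one arm's mean.** With k losses in an arm of 55 and mean improvement m, the shift is (k/55) × m:
- k = 3, m = 2: 3/55 × 2 = 0.11
- k = 5, m = 2: 5/55 × 2 = 0.18
- k = 5, m = 3: 5/55 × 3 = 0.27

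**6. Shift in the between-group difference.** Let Baduanjin improve by b (assumed 0.5 to 2.5) and the combined arm by b + 1.5. With k1 losses in the combined arm and k0 in Baduanjin, the estimate is −(b + 1.5)(1 − k1/55) + b(1 − k0/55).

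| Losses (combined / Baduanjin) | Estimate, b = 0.5 to 2.5 | Shift from −1.5 |
|---|---|---|
| 5 / 0 | −1.32 to −1.14 | 0.18 to 0.36 toward no effect |
| 0 / 5 | −1.55 to −1.73 | 0.05 to 0.23 away from no effect |
| 3 / 2 | −1.41 to −1.37 | 0.09 to 0.13 toward no effect |
| 2 / 3 | −1.45 to −1.49 | 0.05 to 0.01 toward no effect |

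The 0.36 corner requires a 4-point mean improvement in the combined arm, with entry VAS limited to 3–7.

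**7. Benchmark for significance.** With 55 per arm and SD 1.1: 1.98 × 1.1 × √(2/55) = 0.42. The corresponding figure with 44 per arm, 0.47, belongs to 20% loss, where LOCF would not be used.

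**8. Standard error at week 8.** Zeros lying 2 to 3 points from the arm mean widen the spread. The standard error of the arm mean with LOCF (n = 55), against observed cases only, is:
- 3 losses, improvement 2: 0.157 against 0.153
- 5 losses, improvement 2: 0.162 against 0.156
- 5 losses, improvement 3: 0.184 against 0.156

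**9. Responder proportion.** Every imputed zero is a non-responder. If all five losses were in one arm and all would have responded, that arm's proportion would fall by 5/55 = 9.1 percentage points; this is the upper limit.

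Separately, 1.5 and 1.1 with 80% power give 9 per arm, or 12 after 20% loss, and not 55. The steps above take 55 and SD 1.1 as stated and do not depend on how 55 was reached.

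**The case against.** The strongest reply is that the branch will hardly ever be used. At the planned 20% loss its probability is negligible, and in every other case the plan already does what is asked. The rule is also fixed in advance and depends on the amount of missing data, not on results, so it gives the analyst no choice after seeing the outcome. Both points stand, and they limit the size of the finding. They do not give the LOCF branch a purpose: it comes into play only when retention is much better than planned, and then replaces the better method with a weaker one.

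Four stronger readings are tempting, and the document does not support them.
- *Every dropout is scored zero.* No. A participant lost after week 8 keeps the observed week-8 score; only those without a week-8 VAS are affected.
- *Withdrawal for exacerbation automatically means a score of no change.* No. Section 2.5 commits the team to seeking follow-up data, so this applies only where that effort fails.
- *LOCF understates the standard error at week 8.* No. Step 8 shows that it rises in each scenario computed. The fault is a biased value treated as observed.
- *Different visits may be imputed by different methods.* The text speaks of a single dropout rate, and nothing in it suggests a rate for each visit.

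It might also be said that imputation detail belongs in a statistical analysis plan that is not shown. That holds for the imputation model. The LOCF rule and its threshold, however, are stated in the article, so this is a stated choice and not an omission.

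**Conclusion.** The point holds at a modest size. The stated rule, combined with the visit schedule, makes LOCF at the primary time point an assignment of zero change, and a single participant decides whether it applies. With 3 to 5 losses all in one arm and an assumed improvement of 2 to 3 points, the shift is 0.11 to 0.27 points. The largest of these is 18% of the planned 1.5-point difference (0.27/1.5) and about two thirds of the 0.42 points needed for significance. It would not overturn an effect of the planned size, but could matter for one close to the significance boundary. With losses split 3/2 or 2/3 the shift is at most about 0.13. The figures rest on an overall dropout count, SD 1.1, the assumed improvements, and lost participants resembling their arm. The change is worth making because it is nearly free; the trial's validity does not hang on it.

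**What to change.** In section 2.11, delete the LOCF branch and the 5% threshold. State one method for any dropout rate: multiple imputation carried out separately by arm, using baseline VAS, the covariates and the later VAS visits. A likelihood-based mixed model for the repeated VAS scores would serve equally well. A sensitivity analysis that shifts the imputed values in the unfavourable direction for participants withdrawn with worsening pain is optional. The cost is one sentence in the plan and slightly more programming if dropout turns out below 5%. Visits, data collection and clinical procedures do not change.

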**Methods and analysis:**

A total of 110 NCNP patients aged 18 to 50 years will be recruited. Participants will be randomly assigned in a 1:1 ratio to either the TCB group or Baduanjin group. Each group will undergo a total of 16 sessions of therapy over 8 weeks, with two sessions per week. Outcomes will be assessed at week 8, 20, and 32 post-randomization. The primary outcome is the pain intensity at week 8, assessed by the visual analogue scale scores (VAS). Secondary outcomes include functional disability (evaluated with the Neck Disability Index), quality of life (assessed using the 12-item Short Form Survey questionnaire), emotional distress (measured by the Hospital Anxiety and Depression Scale), sleep quality (evaluated with the Pittsburgh Sleep Quality Index), work efficiency (assessed using the Work Productivity and Activity Impairment Questionnaire-Specific Health Problem), and safety. The statistical analyses will follow the two-way repeated measures analysis of variance to compare clinical data between groups across different time points.

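### Repeated-measures ANOVA on unadjusted change scores gives away precision at weeks 20 and 32 and on the secondary questionnaires; a baseline-adjusted mixed model is a cheap improvement

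*Protocol article*

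**What the plan says.** Section 2.11 (Statistical analysis) assigns one method to trends over time and the group-by-time interaction: "two-way repeated measures analysis of variance will be used to compare clinical data at multiple observation time points". The abstract is broader and names nothing else: "The statistical analyses will follow the two-way repeated measures analysis of variance to compare clinical data between groups across different time points".

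Three other statements bear on this.

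- Form of the contrast (section 2.11): "All between-group comparisons will base on the change score of a specific time point and the baseline".
- Baseline adjustment (section 2.11), given for the primary outcome only: "adjusted for baseline VAS and other prespecified covariates using ANCOVA or multiple linear regression if baseline imbalance is observed".
- Missing data (section 2.11): for dropout cases, "last observation carried forward method if the dropout rate is below 5% or the multiple imputation method for a dropout rate of 5% or higher".

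Section 2.1 says that outcomes "will be assessed at weeks 8, 20, and 32". Table 1 adds a baseline measurement of VAS and all five questionnaires, so each has four time points. Section 2.7 plans for 20% loss: "80% power, and a 80% follow-up rate, 55 participants per group were required".

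The article does not say whether baseline is a level of the time factor in the ANOVA, or which ANOVA term answers the treatment question.

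**The concern.** Section 2.11 can be read in two ways, and each has a cost.

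If the comparisons use change scores, the noise in the baseline measurement is subtracted at full weight, although baseline predicts the later score only in part. If baseline is instead a level of time, the group term averages three visits that carry a treatment effect with one that, under randomisation, carries none. The interaction then spreads a sustained benefit over three degrees of freedom. Baseline adjustment, which avoids both losses, is not mentioned for weeks 20 and 32 or for any secondary questionnaire.

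At stake is precision for the maintenance question, which the Discussion presents as a strength of the design, and for the secondary scales. No effect size is stated for either, and effects smaller than the planned week-8 difference are plausible there.

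**Working it through.** **The plan's own figure.** The only power statement, in section 2.7, concerns VAS at week 8: difference 1.5, SD 1.1, two-sided 5%, 80% power, 55 per group. The usual formula gives 2 × (1.960 + 0.842)² × 1.1² / 1.5² = 8.4, so 9 per arm (10 by the exact t-test), or 12 to 13 after 20% loss. The stated 55 is not reproduced. That is a separate matter. Here I take only the planned number of completers, 0.80 × 55 = 44 per arm.

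**Assumptions not in the article.** Equal variance at each visit (set to 1), equal correlation r between any two visits (0.3, 0.5, 0.7), and a treatment effect d = 0.4 SD. If 1.1 is taken as the single-visit SD, d is 0.4 × 1.1 = 0.44 VAS points.

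**Variance per participant and signal for each analysis**

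- Change score at one visit: 2(1 − r); signal d.
- Baseline-adjusted, one visit: 1 − r²; signal d.
- Mean change over weeks 8, 20 and 32: (1 + 2r)/3 + 1 − 2r; signal d.
- Baseline-adjusted mean over the three visits: (1 + 2r)/3 − r²; signal d.
- ANOVA group term with baseline as a level: (1 + 3r)/4; signal (0 + d + d + d)/4 = 0.75d.
- ANOVA interaction with baseline as a level: F test on 3 and 258 df, noncentrality (44/2) × d² × 0.75/(1 − r).

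For the first five, power comes from the noncentral t with noncentrality signal / √(2 × variance / 44).

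**Example at r = 0.5, one visit.** Change score: variance 1.00, noncentrality 0.4/√(2 × 1.00/44) = 1.88, power 46%. Baseline-adjusted: variance 0.75, noncentrality 0.4/√(2 × 0.75/44) = 2.17, power 57%. The variance ratio is 1.00/0.75 = 1.33.

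**Results**

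| Analysis | r = 0.3 | r = 0.5 | r = 0.7 |
|---|---|---|---|
| Variance ratio, single-visit change to adjusted | 1.54 | 1.33 | 1.18 |
| Single visit, change score | 35% | 46% | 67% |
| Single visit, baseline-adjusted | 49% | 57% | 74% |
| Mean of three visits, change | 48% | 62% | 83% |
| Mean of three visits, baseline-adjusted | 80% | 82% | 91% |
| ANOVA group term, baseline as a level | 52% | 42% | 35% |
| ANOVA interaction (3 df), baseline as a level | 33% | 46% | 69% |

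If the ANOVA is run on the three change scores, the group term is not diluted and equals the mean-change row. A constant effect then produces no expected interaction signal, although the interaction is one of the two purposes that section 2.11 gives the ANOVA.

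**At the planned effect.** With a 1.5-point difference and SD 1.1, every analysis in the table has power above 99.9% at all three correlations.

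**Missing data.** A simulation used a true difference of −0.60, with 17% to 19% dropout depending on the week-8 score. Regression imputation by arm, standing in for multiple imputation, gave −0.60 to −0.61 at week 32. Complete cases gave −0.50 to −0.58 at week 8 and −0.60 to −0.65 at week 32.

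**The case against.** The best defence is that section 2.11 does not leave the later visits to pooled ANOVA terms. Its change-score sentence gives a contrast at each visit, with an estimate and standard error that can be pooled over imputations. This stands. A reader might infer that the plan yields no usable visit-wise effect, but the text does not support that.

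A reader might also infer that the ANOVA necessarily dilutes a sustained effect. The 25% loss in the group term arises only if baseline is a level of time. The article never says so, and the change-score sentence points the other way. It would also be wrong to set 42% against 82% at r = 0.5. The first is the group term with baseline as a level, and the second is an adjusted mean over three visits. The like-for-like single-visit figures are 46% and 57%.

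The most tempting stronger reading is bias. The plan imputes dropout cases, and 20% loss would put it in the multiple-imputation branch, which was close to unbiased in the check above when data were missing at random. Shrinkage seen in a completers-only analysis is therefore not a property of this plan. What remains is narrower: imputation is worded only for dropout cases, so a participant who misses week 20 and returns at week 32 is not clearly covered. Nothing says that such a participant is deleted, and intention-to-treat is stated.

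Sphericity corrections and the pooling of F tests over imputations are details that a statistical analysis plan commonly settles, and are not counted here. VAS at week 8 has its own ANCOVA or regression wording, and cervical range of motion has a single post-baseline visit, so neither belongs to this point.

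None of this answers the loss of precision from unadjusted change scores.

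**Conclusion.** The point holds as one of efficiency and clarity. For VAS at weeks 20 and 32 and the five secondary questionnaires, the named analysis is less precise than a baseline-adjusted longitudinal model on either reading of section 2.11. At a single visit the cost is 7 to 14 percentage points of power for a 0.4 SD effect. For a sustained effect averaged over three visits it is 8 to 32 points against mean change. Baseline adjustment was best at every correlation tried.

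These sizes rest on 44 per arm, equal variances and equal correlations of 0.3 to 0.7, none of which except the 44 can be derived from the article. For an effect as large as the planned week-8 difference the choice makes no practical difference to power. Bias is not established. This is a cheap improvement, not an error that threatens the primary result.

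**What to change.** In section 2.11 and the abstract, replace the two-way repeated-measures ANOVA with a linear mixed model for repeated measures, fitted to each outcome:

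- outcomes at weeks 8, 20 and 32;
- fixed effects for arm, visit, arm × visit, baseline score and baseline × visit;
- unstructured covariance;
- all participants with any post-baseline value, which also brings in those who miss a visit and return;
- adjusted between-group difference with 95% CI at each visit.

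Keep multiple imputation as a sensitivity analysis. Amend the change-score sentence to say that comparisons are adjusted for baseline; once baseline is a covariate, the estimated difference is the same for the score and for its change. If a sustained effect is of interest, the average over the three visits can be reported as a contrast from the same model.

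The cost is wording in two places and slightly more programming. No additional data or participants are needed.
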